### Eligibility criteria

#### Inclusion criteria

≥ 65 years of age;ASA grades I ∼ IV;Elective or emergency surgery;Patients undergoing noncardiac surgery;Use of general anaesthesia or regional block anaesthesia.

#### Exclusion criteria

Refusal to provide signed informed consent;Expected length of hospital stay < 3 days;High perioperative troponin levels due to nonischaemic causes (e.g., sepsis, pulmonary embolism, arrhythmia);The same patient can only be included once, regardless of whether the reason for the second operation is related to the first cause.

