**Methods and analysis:**

This prospective, multicentre, real-world observational cohort study will be conducted at 18 designated centres in China from January 2023 to December 2024, with an anticipated sample size of 856 patients aged 65 years and older who are scheduled to undergo noncardiac surgery. The primary outcome will be the incidence of MINS. MINS is defined as a fourth-generation plasma cardiac troponin T (cTnT) concentration ≥ 0.03 ng/mL exhibited at least once within 30 days after surgery, with or without symptoms of myocardial ischaemia. All data will be collected via electronic data acquisition.

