### Study implementation

Before the study begins, each member of the research team will receive thorough instruction on how to correctly administer the MMSE, aCCI, mFI, BI, EQ-5D-3 L, and QoR15. Participants will only be allowed to participate after passing the test. (Supplemental Appendix 1)

**Mini-Mental State Exam (MMSE)**. This scale is simple, widely used and the first choice for dementia screening. Time orientation, place orientation, immediate memory, attention and calculation, delayed memory, language, and visual space are the seven components of the scale. There are a total of 30 questions; 1 point is awarded for each correct response, 0 points for a bad response or no response, and the scale’s overall score range is 0 to 30. The test results and educational level are closely associated. Unliterate > 17 points, primary school > 20 points, and junior high and above > 24 points are the typical cut-offs.**Age-adjusted Charlson Comorbidity Index (aCCI)**. The ACCI is a more widely used scoring system for complications than the CCI is. Complications are quantified based on the number and severity of patients’ diseases and can be used to predict the risk of disease-related death [24].**Assessment of activities of daily living**. The patients will be assessed preoperatively using the Barthel index (BI) evaluation form; 0–40 is classified as severe dysfunction, 41–60 is classified as moderate dysfunction, 61–99 is classified as mild dysfunction, and 100 is classified as self-care.**Preoperative frailty assessment** The mFI is an NSQIP-based 11-factor index that has been shown to adequately reflect frailty and predict mortality and morbidity. The mFI is calculated by dividing the number of factors present in a patient by the number of available factors for which there are no missing data. An mFI score of 0 is classified as healthy, 0-0.21 is classified as prefrail, and ≥ 0.21 is classified as prefrail. The index includes 11 items: nonindependent function or activity status, history of diabetes, history of chronic obstructive pulmonary disease (COPD) or pneumonia, history of congestive heart failure, history of myocardial infarction, angina pectoris, percutaneous coronary intervention (PCI), cardiac surgery, hypertension requiring medication, peripheral vascular disease or static pain, sensory disturbance, transient ischaemic attack (TIA) attack or cerebrovascular accident without sequelae, and cerebrovascular accident with sequelae [25]. In this study, patients with moderate or severe dysfunction and a BI ≤ 60 will be considered positive for item 1.**European Five-dimensional Three-level Quality of Life Scale (EQ-5D-3 L)**. The EQ-5D scale consists of two parts: the EQ-5D-3 L health description system and the EQ-VAS. The EQ-5D-3 L health description system describes five dimensions: mobility, self-care, usual activities, pain/comfort, and anxiety/depression. Each dimension contains three levels. The EQ-VAS records the interviewees’ self-assessed health status on a vertical visual analogue scale, and the two ends of the scale are marked with “the best health status in your imagination” and “the worst health status in your imagination”. The EQ-VAS provides a quantitative description of respondents’ perceptions of their overall health [26].**Diagnostic criteria of MINS**. During noncardiac surgery or within 30 days after surgery, the postoperative troponin level is increased due to myocardial ischaemia (i.e., there is no evidence of nonischaemic causes), and there is no requirement for ischaemic characteristics (such as ischaemic symptoms and ischaemic ECG findings) [27].Quality of Recovery-15 (QoR-15**)**. The QoR-15 is a patient-reported outcome measurement validated to measure the QoR after surgery and general anaesthesia. The BDI ranges from 0 to 150, with a higher score indicating better recovery [28]. The QoR-15 is a smaller version of the QoR-40; the psychometric properties are comparable, but the QoR-15 is more practical to use because it is shorter and takes less time to complete [28, 29]. The following QoR scoring criteria will be used: excellent (QoR-15 > 135), good (122 ≤ QoR-15 ≤ 135), moderate (90 ≤ QoR-15 ≤ 121) or poor (QoR-15 **<** 90).

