
### Exposures, outcomes, and covariates

#### Exposure

Preoperative frailty in geriatric patients.Outcomes of patients followed up 30 days after surgery.

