#### Outcomes

**Primary outcome**

Incidence of MINS. MINS is defined as a peak plasma cTnT concentration of 0.03 ng/mL or greater that is judged to be secondary to myocardial ischaemia (i.e., no evidence of a nonischaemic aetiology causing cTnT elevation, such as sepsis, pulmonary embolism, or myocarditis), which occurs during or within 30 days after surgery. Competent physicians should be informed to further check for ischaemic symptoms, such as myocardial ischaemic symptoms and ECG changes (Supplemental Appendix 1) [13, 30]. Blood samples will be collected before surgery and on the 1st, 2nd and 3rd days after the operation. If a patient has ischaemic symptoms within 30 days after surgery, the researchers will collect blood samples again (Table 2).

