**Secondary outcome**

b)Intraoperative haemodynamic instability and treatment times will also be recorded (Supplemental Appendix 2).c)All-cause mortality within 30 days after the operation (vascular or nonvascular; definitions are provided in Supplemental Appendix 3).d)Length of stay.e)Quality of Recovery-15 (QoR-15).f)Any complications occurred within 30 days after the operation (Supplemental Appendix 4).g)Readmission to the hospital. (Table 2)

**Table 2 Tab2:** Study assessment procedures and timetable

	STUDY PERIOD					
	Enrolment	Allocation	Postoperation			Close-out
TIMEPOINT	***-D1***	**0**	***D1***	***D2***	***D3***	***D30***
ENROLMENT						
Eligibility screen	X					
Informed consent	X					
Allocation		X				
ASSESSMENTS						
MMSE	X					
BI	X					
mFI	X					
aCCI	X					
Primary outcome						
MINS		X	X	X	X	X
Secondary outcomes						
QoR-15			X	X	X	
Postoperative complications			X	X	X	X
30-day all-cause mortality			X	X	X	X
30-day readmission			X	X	X	X

MMSE, Mini-Mental State Examination; BI, Barthel Index; mFI, modified frailty index; aCCI, age-adjusted Charlson Comorbidity Index; QoR-15, Quality of Recovery-15.

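### The nonischaemic-troponin exclusion is not limited to the preoperative sample, so it can remove patients after surgery whom the outcome definition keeps as non-MINS

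*Protocol article*

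**What the plan says.** Four places in the protocol article bear on a patient whose troponin rises for a nonischaemic reason.

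- **Exclusion criteria:** the list includes "High perioperative troponin levels due to nonischaemic causes (e.g., sepsis, pulmonary embolism, arrhythmia". The window is perioperative, and nothing narrows it to the preoperative sample.
- **Primary outcome:** MINS is "a peak plasma cTnT concentration of 0.03 ng/mL or greater that is judged to be secondary to myocardial ischaemia", with the gloss "no evidence of a nonischaemic aetiology causing cTnT elevation, such as sepsis, pulmonary embolism, or myocarditis". Sampling is before surgery, on days 1, 2 and 3, and again on ischaemic symptoms within 30 days.
- **Study implementation (diagnostic criteria of MINS):** "the postoperative troponin level is increased due to myocardial ischaemia (i.e., there is no evidence of nonischaemic causes". This agrees with the Primary outcome section.
- **Abstract, Methods and analysis:** a cTnT "concentration ≥ 0.03 ng/mL exhibited at least once within 30 days after surgery, with or without symptoms of myocardial ischaemia". Ischaemic attribution is not mentioned.

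The exposure is "Preoperative frailty in geriatric patients", which is fixed before surgery. The secondary outcomes include all-cause mortality within 30 days, length of stay, readmission, and "Any complications occurred within 30 days after the operation".

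**The concern.** Take a patient enrolled before surgery who develops sepsis on day 2 and whose cTnT then passes 0.03 ng/mL for that reason. Under the exclusion criteria this patient leaves the study. Under the two body definitions of MINS the patient stays and is a non-event. The two rules give different denominators, and no section reconciles them.

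The Covariant section gives the main purpose as the incidence of MINS in frail patients. That is an absolute proportion, so its denominator matters directly. An exclusion triggered during follow-up also selects the cohort on something that happened after exposure. This sits badly with the Kaplan-Meier and Cox analyses planned from surgery onward.

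The patients at risk of removal are septic, embolic or arrhythmic. If they are dropped altogether, their deaths, complications, long stays and readmissions go with them. If such rises are commoner in frail patients, the comparison between the groups is biased as well.

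**Working it through.** **The plan's own figure.** From Sample size calculation: 15% MINS in frail and 5% in non-frail patients, two-sided α = 0.05, and a 90% figure that the section labels a confidence interval but that works as power. The stated groups of 114 and 570 are in a 1:5 ratio.

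- Pooled proportion: (0.15 + 5 × 0.05)/6 = 0.0667.
- Uncorrected n (frail): [1.960 × √(0.0667 × 0.9333 × 1.2) + 1.2816 × √(0.15 × 0.85 + 0.05 × 0.95/5)]² / 0.10² = (0.5356 + 0.4743)² / 0.01 ≈ 102.
- With continuity correction: (102/4) × [1 + √(1 + 12/(102 × 5 × 0.10))]² ≈ 114, and 5 × 114 = 570.
- Dropout: 114/0.8 = 142.5, rounded up to 143; 570/0.8 = 712.5, rounded up to 713; total 856.

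The sample size reproduces exactly and is not in dispute.

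**Effect of the exclusion.** Let qF and qN be the proportions of frail and non-frail patients with a postoperative nonischaemic rise. Take MINS as 15% and 5% of all patients.

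- Kept as non-MINS: 15.0% and 5.0%, risk ratio (RR) 3.00, whatever qF and qN are.
- Excluded: 0.15/(1 − qF) and 0.05/(1 − qN), so RR = 3.00 × (1 − qN)/(1 − qF).

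The documents give neither qF nor qN, so all rates below are assumptions.

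| Assumed qF / qN | Frail, excluded | Non-frail, excluded | RR |
|---|---|---|---|
| 2% / 1% | 0.15/0.98 = 15.3% | 0.05/0.99 = 5.1% | 3.03 |
| 4% / 2% | 0.15/0.96 = 15.6% | 0.05/0.98 = 5.1% | 3.06 |
| 6% / 2% | 0.15/0.94 = 16.0% | 0.05/0.98 = 5.1% | 3.13 |
| 10% / 3% | 0.15/0.90 = 16.7% | 0.05/0.97 = 5.2% | 3.23 |
| 5% / 5% | 0.15/0.95 = 15.8% | 0.05/0.95 = 5.3% | 3.00 |

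Exclusion raises both incidences in every row. It raises the risk ratio only when qF exceeds qN.

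**Secondary outcomes.** If a share s of a group's deaths falls among the removed proportion q, true mortality m is reported as m(1 − s)/(1 − q). This is too low whenever s exceeds q. As an illustration only, take m = 5% and q = 10%. With s = 10% the figure is unchanged at 0.05 × 0.90/0.90 = 5.0%; with s = 50% it is 0.05 × 0.50/0.90 = 2.8%. The documents supply none of these inputs.

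**The case against.** The strongest defence is that the criterion was meant for what is known at screening. A blood sample is taken before surgery, Table 2 places the eligibility screen on the day before, and emergency patients, who may already be septic, are eligible. A preoperative nonischaemic elevation is a workable eligibility criterion. A reader might infer that the criterion can only be applied after surgery; the preoperative sample shows otherwise. What stands is that the wording does not confine it to that sample. Informed consent also allows consent within 24 hours after surgery for patients who could not give it beforehand, so screening does not always precede the operation.

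A second defence is that no section says enrolled patients will be dropped from the secondary outcomes, and analysis sets are commonly left to documents not shown here. That is fair, and it is why the loss of those outcomes is a possibility and not an established fact. It does not resolve a conflict between two rules that the article itself states.

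Third, the effect on the primary comparison is small against sampling error. With 114 × 0.15 = 17.1 and 570 × 0.05 = 28.5 expected events, the standard error of log RR is √(1/17.1 − 1/114 + 1/28.5 − 1/570) = 0.288. The 95% interval around 3.0 is therefore about 1.7 to 5.3. A shift to 3.23 lies well inside it. This stands, but the shift is systematic and avoidable.

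Two further readings are tempting. One is a three-way conflict in which the abstract counts the same patient as MINS, which under 10%/3% would give 15 + 10 = 25% and 5 + 3 = 8%. That rests on a condensed abstract alone. Both body definitions require ischaemic attribution, and the abstract's phrase about symptoms does not address cause. The figures also arise only if the exclusion is ignored or confined to preoperative values. The other is that the lists of causes contradict each other, with arrhythmia in one and myocarditis in the other. Both lists are only examples, and the Introduction's account of MINS also names arrhythmias.

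**Conclusion.** The point holds in a limited form. The exclusion as worded covers postoperative nonischaemic rises, while Study implementation and Primary outcome retain those patients as non-MINS. The abstract leaves out the attribution to ischaemia and adds to the uncertainty. Applied as written, the exclusion selects patients on an event after exposure and during outcome follow-up.

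Under assumed rates of 2%/1% to 10%/3%, frail incidence moves from 15.0% to 15.3–16.7% and the risk ratio from 3.00 to 3.03–3.23. With equal rates only the incidences move. A reader might conclude that every outcome is certainly biased against or in favour of frailty. The documents do not support that, because they give no nonischaemic-rise rates by frailty and do not fix the direction. The matter should be fixed because the primary denominator is ambiguous and the 30-day outcomes are exposed, not because a large error in the primary comparison has been shown.

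**What to change.** 1. Reword the exclusion so that it applies only to a nonischaemic troponin elevation documented before surgery.
2. State that all other enrolled patients stay in the denominator of every outcome.
3. State that a postoperative rise judged nonischaemic is coded as no MINS, as the two body definitions already imply, and that the patient's deaths, complications, length of stay and readmissions are counted.
4. Add the ischaemic attribution to the abstract's definition so that it matches the Primary outcome section.

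The cost is a wording amendment, with no change to sample size, sampling schedule or tests. The study began in January 2023. If any patient has already been removed for a postoperative rise, the follow-up data collected should be returned to the analysis set and the number reported by frailty group.

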### Study implementation

Before the study begins, each member of the research team will receive thorough instruction on how to correctly administer the MMSE, aCCI, mFI, BI, EQ-5D-3 L, and QoR15. Participants will only be allowed to participate after passing the test. (Supplemental Appendix 1)

**Mini-Mental State Exam (MMSE)**. This scale is simple, widely used and the first choice for dementia screening. Time orientation, place orientation, immediate memory, attention and calculation, delayed memory, language, and visual space are the seven components of the scale. There are a total of 30 questions; 1 point is awarded for each correct response, 0 points for a bad response or no response, and the scale’s overall score range is 0 to 30. The test results and educational level are closely associated. Unliterate > 17 points, primary school > 20 points, and junior high and above > 24 points are the typical cut-offs.**Age-adjusted Charlson Comorbidity Index (aCCI)**. The ACCI is a more widely used scoring system for complications than the CCI is. Complications are quantified based on the number and severity of patients’ diseases and can be used to predict the risk of disease-related death [24].**Assessment of activities of daily living**. The patients will be assessed preoperatively using the Barthel index (BI) evaluation form; 0–40 is classified as severe dysfunction, 41–60 is classified as moderate dysfunction, 61–99 is classified as mild dysfunction, and 100 is classified as self-care.**Preoperative frailty assessment** The mFI is an NSQIP-based 11-factor index that has been shown to adequately reflect frailty and predict mortality and morbidity. The mFI is calculated by dividing the number of factors present in a patient by the number of available factors for which there are no missing data. An mFI score of 0 is classified as healthy, 0-0.21 is classified as prefrail, and ≥ 0.21 is classified as prefrail. The index includes 11 items: nonindependent function or activity status, history of diabetes, history of chronic obstructive pulmonary disease (COPD) or pneumonia, history of congestive heart failure, history of myocardial infarction, angina pectoris, percutaneous coronary intervention (PCI), cardiac surgery, hypertension requiring medication, peripheral vascular disease or static pain, sensory disturbance, transient ischaemic attack (TIA) attack or cerebrovascular accident without sequelae, and cerebrovascular accident with sequelae [25]. In this study, patients with moderate or severe dysfunction and a BI ≤ 60 will be considered positive for item 1.**European Five-dimensional Three-level Quality of Life Scale (EQ-5D-3 L)**. The EQ-5D scale consists of two parts: the EQ-5D-3 L health description system and the EQ-VAS. The EQ-5D-3 L health description system describes five dimensions: mobility, self-care, usual activities, pain/comfort, and anxiety/depression. Each dimension contains three levels. The EQ-VAS records the interviewees’ self-assessed health status on a vertical visual analogue scale, and the two ends of the scale are marked with “the best health status in your imagination” and “the worst health status in your imagination”. The EQ-VAS provides a quantitative description of respondents’ perceptions of their overall health [26].**Diagnostic criteria of MINS**. During noncardiac surgery or within 30 days after surgery, the postoperative troponin level is increased due to myocardial ischaemia (i.e., there is no evidence of nonischaemic causes), and there is no requirement for ischaemic characteristics (such as ischaemic symptoms and ischaemic ECG findings) [27].Quality of Recovery-15 (QoR-15**)**. The QoR-15 is a patient-reported outcome measurement validated to measure the QoR after surgery and general anaesthesia. The BDI ranges from 0 to 150, with a higher score indicating better recovery [28]. The QoR-15 is a smaller version of the QoR-40; the psychometric properties are comparable, but the QoR-15 is more practical to use because it is shorter and takes less time to complete [28, 29]. The following QoR scoring criteria will be used: excellent (QoR-15 > 135), good (122 ≤ QoR-15 ≤ 135), moderate (90 ≤ QoR-15 ≤ 121) or poor (QoR-15 **<** 90).

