## Methods and analysis

### Study design

This prospective, multicentre, real-world observational cohort trial has been registered with clinicaltrials.gov (version no. YXLL-KY-2022 (089), October 24, 2022) following approval from the First Affiliated Hospital of Shandong First Medical University’s Ethics Committee (NCT05635877). The study will be performed in accordance with the guidelines of good clinical practice and the Declaration of Helsinki [21, 22]. Moreover, this investigation will comply with the standard protocol Item: Intervention Trial Statement Recommendation (SPIRIT) [23].

The trial is being conducted at 18 centres across China (Table 1). The investigation officially began in January 2023, and it is scheduled to be finished in December 2024. The actual start date of the study is January 2023, and the expected completion date is December 2024. There will be a total of 856 participants, of whom 713 will be placed in the non-frailty group and 143 in the frailty group. The study design is shown in Fig. 1.

**Table 1 Tab1:** Trial centres

Centre	Centre
The First Affiliated Hospital of Shandong First Medical University	Shandong Provincial Hospital Affiliated to Shandong First Medical University
Qilu Hospital of Shandong University	Qilu Hospital of Shandong University (Qingdao)
Affiliated Hospital of Qingdao University	Second Hospital of Shandong University
Chinese PLA 960th Hospital	Qingdao Municipal Hospital
Weihai Municipal Hospital	Liaocheng People’s Hospital
Affiliated Hospital of Jining Medical College	Linyi People’s Hospital
Zibo Central Hospital	Yantai Yuhuangding Hospital
Yantai Affiliated Hospital of Binzhou Medical College	Weifang People’s Hospital
Jining First People’s Hospital	Affiliated Hospital of Weifang Medical College

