### Sample size calculation

In this study, the incidence of MINS will be the primary outcome. According to the literature review and pre-experimental results, the incidence of frailty is estimated to be 20%, with a MINS incidence of 15% in the frailty group and 5% in the non-frailty group. A bilateral α = 0.05 will be used with a 90% confidence interval. The sample sizes of the non-frailty and frailty groups have been calculated using the PASS 15.0 program; 570 patients will be included in the non-frailty group, and 114 patients will be included in the frailty group. Considering that the estimated proportion of patients withdrawn or lost to follow-up is 20%, 713 patients will be included in the non-frailty group, and 143 patients will be included in the frailty group; in total, 856 subjects will be included in the study.

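### The printed mFI rule labels its top band prefrail, so no score is classed as frail, and the article text does not say which group the prefrail join

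*Protocol article*

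**What the plan says.** The Protocol article, Study implementation (preoperative frailty assessment), turns the score into categories in one sentence. It calls a score of 0 healthy and continues: "0-0.21 is classified as prefrail, and ≥ 0.21 is classified as prefrail". The score is the number of factors present divided by the number of factors with no missing data, out of 11.

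Every other section works with two groups:

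- Exposure gives only "Preoperative frailty in geriatric patients", with no cut-off.
- Study design gives 856 participants, "of whom 713 will be placed in the non-frailty group and 143 in the frailty group".
- Sample size calculation assumes that "the incidence of frailty is estimated to be 20%, with a MINS incidence of 15% in the frailty group and 5% in the non-frailty group".
- Statistical analysis compares two groups by chi-square test, log-rank test and regression.
- Table 2 lists the mFI at enrolment and an allocation step at time 0, without a rule linking them.

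**The concern.** This sentence is the threshold for the only exposure in the study, and it does not do its job. It sets a cut-off at 0.21 and gives the same label on both sides of it. The design needs a frail category, and the rule produces none.

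The index also has three levels while the design has two groups. No sentence in the article text says whether prefrail patients count as non-frail, count as exposed, or are left out. Data come from 18 centres. If the mapping is not fixed in writing before analysis, centres or analysts could apply it differently, or it could be settled after the MINS results are known.

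**Working it through.** **1. The printed bands against the groups needed**

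| mFI | Label as printed | Group in the design |
|---|---|---|
| 0 | healthy | not stated |
| 0–0.21 | prefrail | not stated |
| ≥ 0.21 | prefrail | not stated; frailty presumably intended |

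With all 11 items available, attainable scores are 1/11 = 0.091, 2/11 = 0.182 and 3/11 = 0.273. One factor puts a patient in the middle band, and three are needed for the top band. The middle band is therefore patients with one or two factors.

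**2. The plan's own sample size**

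Inputs from Sample size calculation: p₁ = 0.15, p₂ = 0.05, two-sided α = 0.05. The stated 90% is described as a confidence interval but works as power. The ratio is r = 570/114 = 5.

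- p̄ = (0.15 + 5 × 0.05)/6 = 0.0667
- n = [1.960·√(6·p̄(1−p̄)) + 1.282·√(5·0.15·0.85 + 0.05·0.95)]² / (5 × 0.10²) = (1.198 + 1.061)²/0.05 ≈ 102.0
- With continuity correction: (n/4)·[1 + √(1 + 2·6/(n·5·0.10))]² = 113.7, rounded up to **114**, and 5 × 114 = **570**
- Dropout of 20%: 114/0.8 = 142.5 → **143**; 570/0.8 = 712.5 → **713**; total **856**

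The stated figures reproduce exactly, as a comparison of two groups. The calculation has no third category.

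**3. What changes if the prefrail are pooled with the frail**

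The documents give neither the prefrail share nor its MINS rate, so both are assumptions here. Keep the planned 684 evaluable patients: 114 frail at 15% (17.1 events) and 570 others averaging 5% (28.5 events). Let m of the 570 be prefrail with MINS rate q. Then:

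- exposed rate = (17.1 + q·m)/(114 + m)
- unexposed rate = (28.5 − q·m)/(570 − m)
- power = Φ{[d − 1.96·√(p̄(1−p̄)(1/n₁ + 1/n₂))] / √(p₁(1−p₁)/n₁ + p₂(1−p₂)/n₂)}, without continuity correction, where d is the difference between the two rates

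As planned (114 at 15%, 570 at 5%), d = 10 points and power is 92.5%.

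Example with m = 285 and q = 5%: the exposed rate is (17.1 + 14.25)/399 = 7.86%, the unexposed rate is 5%, and d = 2.86 points. Power = Φ[(0.0286 − 0.0379)/0.0187] = 30.8%.

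Each cell gives the difference in points, then power:

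| Prefrail share of the 570 | q = 5% | q = 6% | q = 7% |
|---|---|---|---|
| 25% | 4.4; 60.9% | 5.3; 75.5% | 6.2; 86.3% |
| 50% | 2.9; 30.8% | 4.6; 66.6% | 6.3; 92.1% |
| 75% | 2.1; 12.1% | 5.9; 78.3% | not possible (negative healthy rate) |

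The difference being estimated shrinks in every cell, from 10 points to between about 2 and 6. Power runs from 12% to 92%. It is lowest where the prefrail are assumed to carry no more risk than the healthy, and close to the planned value where a risk gradient is assumed.

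**The case against.** The strongest reply is that this is a one-word typing error. A threshold between two identical labels serves no purpose, the sentence climbs from healthy through prefrail and needs a worse level, and other sections name a frailty group. That is very likely right. The placing of the prefrail can then be inferred too: the comparison is frailty against non-frailty, a prefrail patient is by ordinary meaning not frail, eligibility has no frailty restriction, and 713 + 143 = 856 leaves nobody out. All of this stands as inference. It does not replace a stated rule. Nor do the planned numbers settle the matter, because 143/856 is 16.7% frail while the text assumes 20%.

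Fig. 1 and the supplementary appendices are not shown and may hold the grouping. The point is therefore limited to the article text. The mislabelled band is wrong whatever they contain.

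Some stronger readings are tempting and are not supported:

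- **That the study will have no frailty group.** This follows only from the literal wording. It does not predict what the centres will do.
- **That power collapses to some particular low value.** This needs someone to pool the bands, and it needs an assumed band size and an assumed absence of risk gradient. The documents supply none of these.
- **That the shared edge at 0.21 misclassifies patients.** It affects nobody. A score of exactly 21/100 cannot arise from 11 or fewer items, and the upper band claims that value explicitly. The shared edge at 0 is likewise settled by the explicit healthy label.

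**Conclusion.** The point holds for the article text. The only printed rule that converts an mFI score into a category classes no score as frail, although the exposure, sample size and analyses all rest on a frailty split. Correcting the probable slip supplies a frail band but leaves the prefrail band unassigned except by inference.

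In size, this is an error in the definition of the sole exposure, and it should be corrected before analysis. Under the planned rates, pooling the prefrail with the frail would replace the 15% against 5% contrast with a smaller one, under every assumption tried. How far power would fall cannot be stated from the documents, and no single figure should be quoted. The conclusion does not rest on the power range. It rests on the printed wording and on the absence of a mapping from three bands to two groups in the text shown.

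**What to change.** In Study implementation, restate the bands so that they are exclusive and the top one is named: mFI = 0 healthy; 0 < mFI < 0.21 prefrail; mFI ≥ 0.21 frail.

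In Exposure, state that the frailty group is mFI ≥ 0.21 and the non-frailty group is mFI < 0.21, that is, healthy plus prefrail. This keeps the protocol's own cut-off and the two groups that were sized. Check that Fig. 1, the supplementary appendices and the derived field in the data capture system say the same, and date the correction before the MINS data are analysed.

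The cost is two sentences and one derivation check, with no new data and no change to the sample size. A three-level analysis across the bands would be an optional extra and is not needed to correct the error.
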